## Introduction

### Background

Endoscopic retrograde cholangiopancreatography (ERCP) is a significant minimally invasive diagnostic and therapeutic procedure extensively used in the diagnosis and treatment of pediatric hepatobiliary disorders, including common bile duct stones, biliary strictures, biliary fistulas, and chronic pancreatitis [1-3]. Research indicates that children undergoing ERCP experience varying degrees of postoperative gastrointestinal dysfunction, including delayed passage of flatus and stool, abdominal distension, nausea, vomiting, and diminished bowel sounds [2,4]. If not promptly addressed, these complications may lead to severe outcomes, such as intestinal perforation and pancreatitis [5]. Postoperative gastrointestinal dysfunction not only increases the child’s discomfort but may also prolong hospital stays, raise intravenous nutrition requirements, and heighten the risk of complications, ultimately impacting the overall recovery process and exacerbating the economic burden on health care systems [6,7].

The mechanisms contributing to gastrointestinal dysfunction following ERCP are multifactorial, encompassing preoperative anxiety, opioid use, mechanical stimulation of the intestines from surgical procedures, vagal nerve dysfunction, and postoperative inflammatory responses [8-10]. Furthermore, the gastrointestinal development of children is incomplete, and their metabolic and neuroregulatory functions are more sensitive than those of adults, potentially exacerbating the delay in postoperative gastrointestinal recovery [11,12]. Current postoperative management strategies have shown limited effectiveness in the pediatric population. For instance, the administration of low-dose opioids after gastrointestinal surgery fails to alleviate postoperative pain and is associated with an increased incidence of postoperative gastrointestinal dysfunction [9]. Currently, there is no efficient, safe, and adherence-friendly specific protocol specifically designed to enhance gastrointestinal function in children after ERCP, highlighting the pressing need to explore nonpharmacological, low-risk alternative therapies.

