### Participants

Participants will be recruited from children who have undergone ERCP in the pediatric department of Shanghai Shuguang Hospital. Inclusion criteria are as follows: (1) aged between 2 and 12 years, (2) having completed ERCP, (3) deemed suitable for pediatric acupressure and external mirabilite application, (4) having provided written informed consent by legal guardians, and (5) having provided age-appropriate assent from the child. Exclusion criteria are as follows: (1) history of abdominal surgery or severe gastrointestinal dysmotility; (2) concomitant failure of vital organs, such as the heart, lung, or kidney; (3) known allergy to mirabilite or skin lesions contraindicating topical application; (4) cognitive or behavioral impairment that would compromise cooperation with acupressure; and (5) intraoperative conversion to open surgery due to major complications, such as perforation or severe bleeding. Participants will be withdrawn under the following circumstances: (1) voluntary withdrawal by the child or their parent; (2) loss of communication during the intervention that precludes further assessment; or (3) the occurrence of a serious adverse event, including marked clinical deterioration or an acute medical condition.

Eligible children will be identified through an electronic medical record system, with 2 senior physicians independently evaluating their enrollment criteria. In the event of disagreement, a third expert will adjudicate. All participants will have the research protocol thoroughly explained by a dedicated research nurse before surgery, and informed consent will be obtained from the guardians and the children.

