### Outcome Measures

#### General Sociodemographic Data

To characterize the study population and assess potential confounding factors, we will collect basic demographic and clinical information from pediatric patients before the intervention, including age, gender, height, weight, and BMI, as well as disease diagnosis, specific indications for undergoing ERCP, history of abdominal surgeries, comorbidities, relevant family medical history, the number of previous ERCP procedures, guardians’ educational level, annual family income and the type of residence (urban or rural). Annual family income will be categorized as: <CNY ¥50,000 (US $7183), CNY ¥50,000-100,000 (US $7183-14,366), CNY ¥100,000-200,000 (US $14,366-28,731), and >CNY ¥200,000 (US $28,731).

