### Data Analysis

Statistical analyses will be performed using SPSS (version 25.0; IBM Corp) and RStudio (Posit PBC), incorporating the *survival* package. A 2-sided significance level of .05 will be applied for all tests, and an intention-to-treat analysis will be implemented to handle missing data.

Categorical baseline variables will be summarized as frequencies and percentages, with group comparisons conducted using chi-square tests or Fisher exact tests as appropriate. Continuous variables will be described as mean with SD if normally distributed and compared via 1-way ANOVA; nonnormally distributed variables will be presented as median with IQR and compared using the Kruskal-Wallis *H* test. Time-to-event analysis will be applied to the primary outcomes, namely time to first flatus and time to first defecation. Cumulative event rates will be visualized using Kaplan-Meier curves, and overall, between-group differences will be assessed via the log-rank test. To address multiple comparisons, a prespecified hierarchical contrast approach will be used. Primary contrasts, including each intervention group compared to the routine care group, will be evaluated using a Bonferroni-adjusted significance threshold of .0167. Exploratory pairwise contrasts between the combination group and each monotherapy group will be conducted only if significant differences are observed in the primary contrasts. Additionally, a Cox proportional hazards regression model will be used to estimate adjusted hazard ratios with 95% CIs for each intervention relative to routine care while controlling for baseline covariates identified in univariable analysis with a *P* value of <.10.

The secondary outcome analysis will include comparisons of PONV incidence using chi-square tests, with Bonferroni-adjusted pairwise testing where applicable. Inflammatory markers, including WBC count and serum amylase, will be analyzed using repeated-measures ANOVA to evaluate changes at 3 hours after surgery and on the morning of postoperative day 1. Safety outcomes will be summarized descriptively, and between-group differences in adverse events will be examined using chi-square or Fisher exact tests.

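### The covariates for the adjusted hazard ratios are chosen by a univariable P<.10 screen of the trial's own data, so the effect estimate partly depends on chance selection

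*Protocol article*

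**What the plan says.** In the Data Analysis section, the two primary outcomes are first shown by Kaplan-Meier curves, and "between-group differences will be assessed via the log-rank test". The three contrasts against routine care "will be evaluated using a Bonferroni-adjusted significance threshold of .0167". The section then adds that "a Cox proportional hazards regression model will be used to estimate adjusted hazard ratios with 95% CIs for each intervention relative to routine care", "controlling for baseline covariates identified in univariable analysis", with P<.10 as the cut-off.

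The section does not say which variables enter the screen or define the univariable analysis. The obvious pool is the list under General Sociodemographic Data, which names 14 items: age, gender, height, weight, BMI, diagnosis, ERCP indication, abdominal surgery history, comorbidities, family medical history, number of previous ERCPs, guardians' education, family income and type of residence. Preoperative WBC count and serum amylase (Secondary Outcomes) would make 16.

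**The concern.** The log-rank test gives a P value and the Kaplan-Meier curves are a display. The adjusted hazard ratio is therefore the only effect estimate with a confidence interval that the article states for the primary outcomes, and Study Aims makes efficacy against routine care a primary objective. That estimate is tied to a rule whose result is unknown until the outcome data are analysed.

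In a randomised trial, confounding is dealt with in expectation. Covariate adjustment mainly serves to gain precision from factors that predict the outcome. A significance screen serves this badly in a small trial: it lets in variables that look prognostic by chance and can shut out variables that are prognostic. Run once per outcome, it can also leave flatus and defecation adjusted for different things. This is a rule that the article states, so it is not a detail left to an unseen analysis plan.

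**Working it through.** **The plan's own figures.** A four-group F test with f = 0.593, α = .05 and power .95 needs N = 53 (power .950). Equal groups give 56 (power .962), as stated under Sample Size. Then 56/0.80 = 70, or 72 in multiples of four. The contrast threshold is .05/3 = .0167. All agree with the article, and none depends on the Cox model.

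**Chance that a noise covariate enters.** For m independent candidates unrelated to the outcome, P(at least one with P<.10) = 1 − 0.9^m, and the expected number is 0.1m.

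| m | Why this m | P(at least one) | Expected number |
|---|---|---|---|
| 10 | allows for correlation among age, height, weight and BMI | 65% | 1.0 |
| 13 | 14 listed, less surgery history (an exclusion) | 75% | 1.3 |
| 14 | all listed | 77% | 1.4 |
| 16 | with preoperative WBC and amylase | 81% | 1.6 |

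The chance passes one half at m = 7 (1 − 0.9^7 = 52%). A simulation of 343 null trials with n = 72 and 14 candidates gave 77% and a mean of 1.5.

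**Chance that a real factor is dropped.** The documents give no prognostic strengths, so those used here are assumptions. With d events and a two-sided test at .10 (z = 1.645), the probability of passing is Φ(√d · ln HR − 1.645) for a continuous factor (HR per SD) and Φ(√(d/4) · ln HR − 1.645) for a 50:50 binary one.

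| Assumed factor | Missed, 72 events | Missed, 56 events |
|---|---|---|
| Binary, HR 1.5 | 47% | 55% |
| Binary, HR 2.0 | 10% | 17% |
| Continuous, HR 1.3 per SD | 28% | 37.5% |
| Continuous, HR 1.5 per SD | 4% | 8% |

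Example: √18 × 0.405 − 1.645 = 0.075, Φ = .53, so 47% are missed.

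**Effect on the estimate.** Simulated trials had 13 independent candidates, one of them prognostic (HR 1.3 to 1.5 per SD), a treatment HR of about 2 and no censoring.
- The prognostic factor was dropped in 11% to 38% of trials at 18 per arm and 18% to 46% at 14 per arm. This is somewhat more than the formula gives, as would be expected when the screen leaves treatment out.
- The screened treatment hazard ratio differed by more than 10% from the one adjusted for the right factor in 32% to 39% of arm estimates at 18 per arm and 43% to 47% at 14 per arm.

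**Effect on error rates.** With 14 candidates, one at log HR 0.4 per SD:
- Family-wise error of the Cox arm terms tested at .0167 was .069 screened against .065 prespecified (18 per arm), and .065 against .059 (14 per arm). With 4,000 trials each figure has a standard error of about √(.067 × .933/4000) = .004.
- Coverage of the 95% CI under no effect was 93.7% screened against 94.1% prespecified (18 per arm), and 92.0% against 93.0% (14 per arm).

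**The case against.** The strongest reply is that the primary inference does not use this model. The log-rank contrasts are unadjusted, and the Cox model is introduced as an addition. That stands. A reader might infer that the primary tests are biased or their error rate inflated. The documents do not support this, and even for the Cox terms the differences are within or near simulation error.

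It can also be said that the estimate moves little. The median shift in log HR was about 0.06 at 18 per arm, against a standard error of about 0.35. The 90th percentile, however, was about 0.22. Most trials would be little affected and some noticeably so, with no way to tell which.

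Three further inferences are tempting but do not hold:
- Abdominal surgery history is on the baseline list although "history of abdominal surgery or severe gastrointestinal dysmotility" is an exclusion criterion. If it is constant, it cannot pass any screen, so it does no harm.
- The Background names "preoperative anxiety, opioid use, mechanical stimulation of the intestines from surgical procedures" among the causes of dysfunction, and the baseline list mentions neither opioids nor the procedure's course. But that list is open-ended and the article is condensed, so their absence shows no fault. Pain relief given after randomisation would not be a baseline covariate anyway.
- It would be too strong to say that known prognostic factors are omitted. The documents establish none, and do not say that age within 2 to 12 years or previous ERCPs predict recovery.

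Finally, the univariable analysis could mean baseline comparisons between arms. The model would then not depend on outcomes, but it would still be chosen by chance and would ignore prognostic value.

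**Conclusion.** The point holds for the adjusted hazard ratios and their confidence intervals only. On the natural reading, the adjustment model is fixed after outcomes are seen, may differ between the two primary outcomes, more likely than not admits a noise covariate (about 65% to 77% for 10 to 14 independent null candidates, less if correlation leaves fewer effective ones), and can drop a factor that matters in a trial of 56 to 72 children. The loss is in precision and in an estimate that depends on chance selection, not in the validity of the log-rank tests.

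This rests on independence of the candidates, on assumed prognostic strengths, and on taking the baseline list as the pool. Severity is minor to moderate.

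**What to change.** Before any outcome analysis, delete the P<.10 rule and name a short covariate set chosen on clinical grounds from baseline data already collected. Keep it in the model whatever the P values, and use the same set for flatus and defecation. One example is age as a continuous variable and number of previous ERCPs as 0 versus 1 or more. ERCP indication should be added only if collapsed into a few categories defined beforehand, since sparse levels would be costly with 18 per arm. Report the unadjusted hazard ratio with its 95% CI beside the adjusted one.

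The cost is a change of wording and a few degrees of freedom spent on fixed covariates, some of which may prove uninformative. The sample size of 72 is unchanged. The Results section reports 38 children randomised by January 2026 and no interim analysis, so on that account the change could still be made before outcomes were analysed.

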### Sample Size

G*Power (version 3.1; Heinrich Heine University Düsseldorf) software was used to calculate the sample size. We used the *F* test as the method for statistical analysis, establishing an α of .05 and a power (1–β) of .95. The estimation was based on data from a previous high-quality clinical trial, which used a 3-arm parallel design evaluating combined mirabilite application with massage, massage alone, and mirabilite application alone in patients undergoing laparoscopic hepatectomy [23]. Using the reported group means, a pooled SD of 13.03 hours, and a sample size of 30 per group from that trial, the software estimated an effect size (*f*) of 0.593. On the basis of this effect size, the calculated total sample size required for this 4-group study was 56 participants. To account for an anticipated dropout rate of 20%, the final planned total sample size is 72 participants, with approximately 18 (25%) individuals allocated to each group.

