#### Secondary Outcomes

##### Overview

To comprehensively evaluate postoperative recovery and investigate potential mechanisms, the subsequently mentioned secondary outcomes will be monitored. The first outcome is the incidence of PONV. The frequency of PONV episodes will be recorded every 4 hours. The second outcome is postoperative inflammatory markers. To establish baseline values and track the perioperative inflammatory trajectory, venous blood samples for quantification of WBC count and serum amylase levels will be collected before surgery, at 3 hours after surgery, and on the morning of postoperative day 1. These parameters will serve to assess pancreatic functional recovery, screen for complications, and gauge the magnitude of the systemic inflammatory response. Furthermore, they will provide indirect indicators of gastrointestinal functional status, offering valuable reference data for monitoring postoperative clinical progression.

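### Repeated-measures ANOVA for WBC count and serum amylase becomes a complete-case analysis unless missing values are imputed, and intention-to-treat does not fill that gap

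*Protocol article*

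**What the plan says.** Under Data Analysis the method for the two markers is fixed: "Inflammatory markers, including WBC count and serum amylase, will be analyzed using repeated-measures ANOVA to evaluate changes at 3 hours after surgery" and on the following morning. The same section deals with missing data in one clause: "an intention-to-treat analysis will be implemented to handle missing data". It names SPSS 25.0 and RStudio as software. No imputation method or likelihood-based model for incomplete series appears anywhere in the article.

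Under Secondary Outcomes (Overview), blood samples "will be collected before surgery, at 3 hours after surgery, and on the morning of postoperative day 1". Table 1 places randomization after surgery, so the pre-surgery draw comes before it.

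Sample Size allows for 20% dropout overall. Participants lists grounds for withdrawal, among them "the occurrence of a serious adverse event, including marked clinical deterioration or an acute medical condition". Quality Control and Precautions adds that continued refusal or marked distress during an intervention ends the session or leads to withdrawal.

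**The concern.** The two statements in Data Analysis do not fit together once a sample is missing. Intention-to-treat defines the analysis set and the arm in which each child counts. It does not say what value stands in for an absent one. Standard repeated-measures ANOVA, as in the SPSS repeated-measures GLM procedure, needs all of a child's analysed samples. A child with a 3-hour value but no day-1 value is removed at both times, and the 3-hour value is discarded.

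Removal of this kind is harmless to the estimate if loss has nothing to do with the markers. Two features of the protocol make a link conceivable. Withdrawal for deterioration may go with high WBC or amylase, since the protocol uses these markers to screen for complications. Refusal of massage or paste can arise only in the three active arms, so loss may differ by arm. If children with high 3-hour values were lost more often from active arms, the remaining children would look less inflamed there without any treatment effect. The Discussion intends to use these markers as preliminary evidence of an anti-inflammatory mechanism.

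**Working it through.** **The plan's own figure.** Sample Size describes "establishing an α of .05 and a power (1–β) of .95" and reports that the software "estimated an effect size (*f*) of 0.593". For a one-way F test with 4 groups and noncentrality f² × N, N = 56 gives power 0.9615 and N = 52 gives 0.9459, so 56 is the smallest balanced total. Allowing for dropout, 56 / 0.80 = 70, rounded up to 18 per group = 72. The figure reproduces; nothing here turns on an error in it.

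**Children kept under complete-case deletion.** If the whole 20% allowance meant a missing marker sample, 72 × 0.80 = 57.6 children would remain (14.4 per arm). At 5% loss, 72 × 0.95 = 68.4 (17.1 per arm). The true rate is not in the document, so 5% to 20% is an assumed range.

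**Bias if loss is informative.** Assumptions: three samples per child in SD units, correlation 0.6 between any two, no treatment effect, 200,000 simulated children per setting. The day-1 sample is missing with probability 1 / (1 + exp(-(a + b × 3-hour value))), with a chosen to give the stated loss and b the log-odds per SD. Shift in the arm's complete-case mean, in SD:

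| Loss | b | Pre-surgery | 3 hours | Day 1 |
|---|---|---|---|---|
| 5% | 0.75 | -0.023 | -0.037 | -0.023 |
| 5% | 1.5 | -0.041 | -0.069 | -0.042 |
| 20% | 0.75 | -0.081 | -0.135 | -0.083 |
| 20% | 1.5 | -0.136 | -0.230 | -0.138 |

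With b = 0 all shifts are zero apart from simulation noise. An estimate of the day-1 mean that uses the earlier values of all children, valid when loss depends only on observed values, stays within 0.004 SD of zero in every setting.

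**What this does to a test.** Compare a control arm of 18 with an active arm of 14.4 on day 1. The standard error is √(1/18 + 1/14.4) = √0.125 = 0.354 SD. A bias of 0.08 to 0.14 SD is 0.23 to 0.40 standard errors, which raises a two-sided 5% error rate to about 5.6% to 6.8% (normal approximation). At 5% loss the standard error is √(1/18 + 1/17.1) = 0.338, and a bias of 0.02 to 0.04 SD gives about 5.0% to 5.2%.

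**Means versus changes.** The table shows shifts in means. With equal correlations the pre-surgery mean of the retained children moves as well. At 20% loss the change from pre-surgery to day 1 is therefore almost unbiased: -0.083 - (-0.081) = -0.002 and -0.138 - (-0.136) = -0.002. The change to 3 hours shifts by -0.135 - (-0.081) = -0.054 to -0.230 - (-0.136) = -0.094. The size of any bias thus depends on which contrast is read.

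**If loss follows the unseen day-1 value.** I repeated the simulation with loss depending on the day-1 value itself (correlation 0.5 to 0.6, 20% loss, b of 0.75 to 1.5). About 57% to 71% of the complete-case bias then remains in the estimate that assumes loss depends only on observed values.

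**The case against.** The strongest reply is that the article ties intention-to-treat to missing data on purpose and leaves the mechanics to a fuller document. If values are imputed first, repeated-measures ANOVA runs on all 72 children. That is possible, so deletion cannot be stated as a certainty. What stands is that the article names both a method and a missing-data approach, and the second does not repair the first.

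Other parts of the reply hold and limit the point:

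- A reader might take the 20% as the rate of lost blood samples. It is an overall dropout allowance, and the last draw is on the morning after the procedure, so sample loss may be much lower.
- A reader might assume 10% missing at each of three draws, leaving 72 × 0.9³ = 52.5 children and a clear loss of power. The document gives no basis for that rate, and the pre-surgery draw cannot be lost through withdrawal after randomization.
- A reader might infer that the day-1 comparison will favour the interventions. The document does not show this. Ending a session loses no blood sample, a deteriorating child may well still be tested, and nothing links refusal to marker values. Loss that differs by arm but is unrelated to the values causes no bias.
- A reader might add a sphericity problem. The analysis sentence names two postoperative times, and with two levels sphericity is not in question. It would matter only if all three samples were entered, and the article does not rule out a correction.
- The primary outcomes use time-to-event methods and are untouched.

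**Conclusion.** The point holds as a minor one on two secondary outcomes. Followed as written, and unless values are imputed, the plan gives complete-case analyses of WBC count and serum amylase, which conflicts with its intention-to-treat aim.

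Bias is a possibility. The figures of -0.08 to -0.14 SD on day 1 at 20% loss, and -0.02 to -0.04 SD at 5%, rest on an assumed correlation of 0.6, loss in an active arm driven by the 3-hour value, and no loss in the comparator. The consequence for the error rate is small even at 20% loss, and it vanishes if loss is unrelated to the markers. The documents do not support a claim that the results will be biased, or that a fifth of the samples will be lost.

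**What to change.** Replace repeated-measures ANOVA with a linear mixed model for repeated measures, fitted by REML to the 3-hour and day-1 values. Use arm, time and arm-by-time as fixed effects, the pre-surgery value as a covariate and an unstructured covariance. Include all randomised children with any available postoperative value, and report the arm contrasts at 3 hours and on day 1. State that the model assumes loss depends only on observed values, and say in the text that intention-to-treat describes the analysis set.

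The cost is a few sentences of analysis wording. No new data are needed, both named packages can fit the model, and the article reports no interim analysis so far, so the change can be made before results are examined.

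The downsides are limited:

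- If loss follows the unseen day-1 value, the model removes only part of the bias.
- If only day-1 samples are missing, there may be no gain in power.
- A child without a pre-surgery value would drop out of a model that uses it as a covariate, so a simple rule for that case should be stated.

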#### Combination Group

This group will simultaneously receive both acupoint massage and external application of mirabilite, adhering to the same protocols as the single-intervention groups, but spaced apart from each other. An interval of at least 1 hour will be maintained between the 2 interventions to avoid interference. The acupoint massage will promote the smooth flow of Qi and blood within the meridians, while the localized stimulation from the external application of mirabilite will further facilitate the recovery of gastrointestinal function and enhance therapeutic effects.

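### WBC count and serum amylase: repeated-measures ANOVA gives the pre-surgery value no covariate role and drops incomplete cases; a baseline-adjusted mixed model would be more precise at no extra data cost

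*Protocol article*

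**What the plan says.** The protocol article, Secondary Outcomes (Overview), schedules three draws: before surgery, 3 hours after surgery and the morning of day 1. It gives the first draw a purpose: "To establish baseline values and track the perioperative inflammatory trajectory, venous blood samples for quantification of WBC count and serum amylase levels" are taken. Table 1 also marks a pre-surgery draw for both markers.

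Data Analysis then says that the markers "will be analyzed using repeated-measures ANOVA to evaluate changes at 3 hours after surgery and on the morning of postoperative day 1". It does not mention the pre-surgery value in that sentence, name a covariate, or say whether the group term or the group-by-time term answers the question. Data Collection and Management likewise lists only the two post-surgery times for the inflammatory indicators.

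For missing data, Data Analysis offers only an intention-to-treat analysis. For the primary outcomes the same section does plan a covariate-adjusted model (Cox regression), so adjustment is not foreign to the plan.

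**The concern.** A pre-treatment measurement of the same marker is usually among the best available predictors of the later values. If it is collected and not used as a covariate, precision is given away in a trial with about 18 children per arm.

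The named method adds a second problem. Classical repeated-measures ANOVA needs every included value from a child and deletes the child otherwise. Intention-to-treat defines who is analysed and in which arm. It is not a missing-data method and does not undo that deletion. The plan itself expects 20% dropout and withdraws children who refuse or deteriorate, so incomplete series are foreseeable.

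Third, with no term named, the test could be of the group main effect, which averages the two times. If an effect were present only on day 1, that average would show half of it.

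At stake is the secondary objective on inflammatory markers, which the Discussion wants to use as preliminary evidence on mechanism.

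**Working it through.** **1. The plan's own figure.** The article gives no sample size for the markers. Its only calculation is for the primary outcome: "establishing an α of .05 and a power (1–β) of .95", "the software estimated an effect size (*f*) of 0.593", and "the calculated total sample size required for this 4-group study was 56 participants". For a one-way ANOVA with 4 groups, noncentrality f²N and degrees of freedom 3 and N − 4, the smallest N reaching .95 is 53. Rounded up to equal arms this is 56, with power .962. For the "anticipated dropout rate of 20%, the final planned total sample size is 72 participants", 56/0.8 = 70, and equal arms give 72, or 18 per arm. The stated figures reproduce and are not affected by this point.

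**2. Precision.** The documents give no correlations, so assume equal SDs (set to 1) and one correlation ρ between any two of the three draws, over the range .3 to .7. For the average of the 3-hour and day-1 values, the per-child variance is:

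- unadjusted: (1 + ρ)/2
- change from baseline: (1 + ρ)/2 + 1 − 2ρ
- adjusted for baseline: (1 + ρ)/2 − ρ²

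| ρ | Unadjusted | Change | Adjusted | Adjusted/unadjusted | Adjusted/change |
|---|---|---|---|---|---|
| .3 | .65 | 1.05 | .56 | .86 | .53 |
| .5 | .75 | .75 | .50 | .67 | .67 |
| .7 | .85 | .45 | .36 | .42 | .80 |

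Adjustment therefore cuts the variance by 14%, 33% or 58% against unadjusted values, and by 47%, 33% or 20% against change scores. It is better in every row, whichever reading of the sentence is right.

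**3. Complete cases.** Suppose each draw is independently missing with probability m (an assumption; the article gives no rate by draw). With two draws in the model, the number left is 72(1 − m)²: 65 at m = .05, 58 at .10 and 46 at .20. If the pre-surgery value is also a level of the time factor, it is 72(1 − m)³: 62, 52 and 37.

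**4. Which term is tested.** Take, for illustration only, a 1-SD effect on day 1 and none at 3 hours, 18 per arm, two-sided .05, comparing two arms. By the normal approximation, power = Φ(3δ/σ − 1.96), since √(18/2) = 3.

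| Test | δ | σ² | ρ = .3 | ρ = .5 | ρ = .7 |
|---|---|---|---|---|---|
| Group main effect, two times | 0.5 | (1 + ρ)/2 | .46 | .41 | .37 |
| Group-by-time, two times | 1 | 2 − 2ρ | .72 | .85 | .97 |
| Day 1, adjusted for baseline | 1 | 1 − ρ² | .88 | .93 | .99 |

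Halving occurs only in the first row. The group-by-time term does not average the times, although it too falls below the adjusted day-1 contrast.

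**5. Treatment received by 3 hours.** In the combination arm, "An interval of at least 1 hour will be maintained between the 2 interventions to avoid interference". A massage session covers 6 points (Acupoint Massage Group text) or 7 (Table 2) at 2 minutes each, so 12 or 14 minutes. Adding the 60-minute interval and the 60-minute application gives 132 or 134 minutes, which is less than 180. Table 1 places randomization after surgery, but no section gives the hour of the first session. Exposure at the 3-hour draw therefore cannot be determined from the article.

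**The case against.** The best defence is that the text is ambiguous rather than wrong. It speaks of changes, and the pre-surgery draw is said to establish baseline values. The authors may intend the pre-surgery value as a level of the time factor, or may analyse change from it. Either would use baseline, and a condensed article may leave model terms to a fuller plan. This stands to the extent that a reader should not conclude that baseline is ignored: the article does not say so. It does not rescue the method. The article commits to repeated-measures ANOVA, and the table in step 2 shows adjustment ahead of change scores as well.

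Several stronger readings are tempting and are not supported:

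- *The 3-hour sample is essentially untreated.* The first-session hour is not stated, and a full combination cycle of 132 to 134 minutes could finish before the draw. The single-intervention arms need less time.
- *The analysis halves the effect.* That requires the group main effect to be the tested term and the effect to be absent at 3 hours. The article establishes neither.
- *The gain is 1 − (1 − ρ²), that is 9%, 25% or 49%.* Those figures apply to a single time point against its unadjusted value, not to the two-time average.
- *Amylase is skewed and wrongly left untransformed.* The documents give no distribution and do not rule out a transformation.

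It is also fair that randomization keeps an unadjusted comparison of complete data unbiased, and that the Discussion claims only preliminary mechanistic evidence.

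**Conclusion.** The point holds as one about efficiency and clarity. The named analysis gives the pre-surgery value no covariate role and, in its classical form, deletes incomplete cases in conflict with the stated intention-to-treat principle. The variance given up on the two-time average is 14% to 58% if post-surgery values are unadjusted and 20% to 47% if change scores are used, assuming equal SDs and a common correlation of .3 to .7. The loss of children depends wholly on an assumed missingness rate: about 58 of 72 remain at 10% per draw with two draws.

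The dilution argument is conditional, for the reasons above, and is best read as a reason to name the contrast. The consequence is mainly lost precision. Bias would arise only if the deleted children differ systematically, for example those withdrawn after deterioration, and the documents cannot settle that. A change is worthwhile but does not bear on the trial's main conclusion.

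**What to change.** Replace the repeated-measures ANOVA with a mixed model for the 3-hour and day-1 values, fitted separately for WBC count and amylase. Include arm, time, arm-by-time and the pre-surgery value as covariate, and every child with at least one post-surgery value. Name the day-1 arm difference as the key contrast, and state how a missing pre-surgery value will be handled so that it does not itself remove a child. A log scale for amylase, reported as ratios, is optional if the values prove skewed.

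The cost is a few sentences of analysis text and a different procedure in the software already named. No new data or extra children are needed. Recruitment is ongoing and the article reports no interim analysis, so the change can still be specified before any results are seen.
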